## Abstract

**Background:**

The clinical demand for reirradiation is increasing; however, evidence for dose guidance to estimate normal tissue toxicity is lacking. The goal of the REPAIR trial is to determine the maximally tolerated dose (MTD) of reirradiation in the thorax, implemented by sequentially increasing the normal tissue recovery factors applied to previously delivered dose.

**Methods:**

This multi-institution phase I dose-escalation study for patients undergoing thoracic reirradiation will use a time-to-event continual reassessment method (TITE-CRM). The MTD of reirradiation in this trial is represented by the recovery factor equation associated with a 35% or lower rate of Common Terminology Criteria for Adverse Events (CTCAE) grade 3–5 treatment-related toxicity occurring within 1 year of treatment. Accrual will start at level 1 (recovery factor = 10% at 6 months + 0.75% per month thereafter). Patients (n = 48) will be assigned to recovery factors using the TITE-CRM model. The model will use all available information from previously accrued patients to assign the highest dose with a predicted risk of grade 3–5 toxicity of 35% or less. Patients with recurrence, metastasis, or new primary malignancies in the thorax requiring radiation and who have previously received radiotherapy to the thorax, where reirradiation is expected to exceed the dose constraints used for de novo treatments, are eligible.

**Discussion:**

This study will provide information on the safety of dose escalation for thoracic reirradiation using the concept of recovery after radiation.

**Trial Registration:**

Clinicaltrials.gov identifier: NCT06558175 (registration date August 14, 2024).

## Background

Interest in cancer re-treatment with radiotherapy (reirradiation) is increasing [1, 2]. Reirradiation may be used to treat recurrent, metastatic, or new primary malignancies, and benefits range from palliation to cure. The practice is endorsed by international experts and professional societies [2–6]; however, significant uncertainty remains regarding the safe dose limits in this context.

Prospective clinical evidence to predict toxicity in the setting of reirradiation is lacking. The most comprehensive data exists for re-treatment involving spinal cord where normal tissue tolerance increases by at least 20–25% at 6 months following the first course of radiation [7–11]. Reports also exist for reirradiation in specific sites with defined first and second courses, such as in recurrent head and neck and brain [12]; however, it is hard to translate this data into various re-treatment scenarios involving other organs and different dose/fractionation schemes. Some groups have published cumulative dose constraints for reirradiation based on combinations of literature review, expert opinion, and experience, but these are not based on strong levels of evidence [13–15]. There is an unmet need for prospective clinical trials to determine safe dose limits for reirradiation.

Physicians are left with little guidance on how to perform reirradiation. Safe dose limits are critical because overdosing organs-at-risk (OAR) risks toxicity in patients for whom treatment goals may vary substantially: from symptom relief/prevention to local control, prolonging survival, or even cure. Reirradiation is often dose-limited by concerns over normal tissue toxicity based on the dose limits defined in the de novo setting. Maintaining accumulated dose from current and prior treatments below the de novo OAR dose limits is a safe approach from the perspective of preventing radiation-induced toxicity; however, this is usually not feasible and therefore (sometimes severely) limits the dose that can be offered for reirradiation. For some patients, this means de-escalating to less dose than what they could benefit from and for others this might mean no further radiation is pursued at all. Risk aversion rooted in the principle of non-maleficence, even with inaction may lead to worse outcomes from cancer progression.

Much is still unknown about the magnitude and timeline of radiation injury recovery in most organs; nevertheless, assuming some level of organ recovery after prior radiotherapy and applying forgiveness against previously delivered dose makes reirradiation within standard dose limits feasible. Practice varies widely on application of this principle and implementation becomes more art than science [1, 2, 4]. Several retrospective studies and reviews have described acceptable toxicity profiles with high-dose thoracic reirradiation; however, sufficient information regarding dose metrics and dose accumulation is unavailable, which precludes reproducible implementation in general practice [16–25].

The REPAIR trial endeavors to identify the magnitude of radiation recovery in the thorax and enable safe reirradiation dose escalation. The trial will provide critical information to support shared-decision making and ensure the risk–benefit trade-offs of reirradiation align with each patient’s wishes. In addition, the data from this study will be informative in guiding subsequent studies on the use of reirradiation for other sites (such as the brain, abdomen, and pelvis) and to inform future re-irradiation trials. The objective of this phase I study is to determine the safety of dose escalation via recovery factors applied against previously delivered dose for patients receiving thoracic reirradiation.

## Methods

### Study design

This study will use a time-to-event continual reassessment method (TITE-CRM). The study design is based on previous thoracic dose escalation trials, including RTOG 0813 and SUNSET [26, 27]. Dose will be escalated by allowing increasing amounts recovery (or “forgiveness”) for previously delivered radiation (Table 1).

**Table 1 Tab1:** Recovery factor equations to be applied against previous dose(s)

Level	Recovery After 6 Months	+ Rate/Month
−1	3%	0.50%
0	10%	0.50%
**1**	**10%**	**0.75%**
2	15%	0.75%
3	15%	1.00%
4	20%	1.00%
5	20%	1.25%
6	25%	1.40%

+ Rate/month is additional recovery for every month thereafter

### Sample size justification and feasibility

In general, TITE-CRM trials require a sample size that is equal to the number of dose levels in the study, multiplied by 6 [28]. In this trial, with 8 dose levels, the sample size will be 48. Given the multi-institutional nature of this study, we estimate that there will be 12–16 patients accrued per year and recruitment will be completed over 36–48 months.

### Objectives

#### Primary endpoints

The primary endpoint of this study is the maximally tolerated dose (MTD) to normal tissues undergoing thoracic reirradiation, implemented by sequentially increasing the normal tissue recovery factors applied to previously delivered dose. The MTD is the recovery factor equation associated with a ≤ 35% rate of grade 3–5 pre-specified treatment-related toxicity occurring within 1 year of treatment.

#### Secondary endpoints

Toxicity, progression of treated disease, distant metastases, progression-free survival, overall survival, patient reported outcomes and quality of life.

### Patient selection

#### Inclusion criteria

Pathologically (histologically or cytologically) proven diagnosis of malignancy, with disease in the thorax requiring reirradiation for any treatment intent. This may include primary lung cancer of any type, esophageal cancer, recurrences, and/or metastasis from any primary. The intrathoracic disease at the time of enrollment does not itself require a biopsy if a prior biopsy has been obtained at that location or another body site. If the risk of biopsy is unacceptable and there is no prior confirmation of malignancy even at the time of the initial course of radiation, enrollment is permitted provided that the case is discussed at a multidisciplinary tumor board or peer-review rounds.Must have received prior photon thoracic radiotherapy ≥ 6 months agoLife expectancy > 6 months.Eastern Cooperative Oncology Group (ECOG) performance status 0–2Age ≥ 18 yearsThe current radiation course, when added to the previous radiation doses, exceeds the normal tissue constraints used for de novo treatments for esophagus, heart, lungs, trachea, bronchus, great vessels, or brachial plexus. Forgiveness of the previous dose (i.e. reduction of the previous dose in the cumulative dose calculation) is required to meet constraints. Submission of a pre-plan summary showing the estimated accumulation of current and previously delivered doses is required for registration.

#### Exclusion criteria

Persistent toxicity from previously delivered radiation therapy.Prior development of symptomatic radiation pneumonitis or immunotherapy-related pneumonitis from previous treatment, even if resolved.Cumulative radiation dose for all organs-at-risk is already below dose constraints without a recovery factor applied, or with a recovery factor less than the current dose level of the trial. This will be confirmed by the enrolling team after the planning is completed.The reirradiation dose-limiting structure is expected to be spinal cord, chest wall, and/or stomach; this protocol is not meant to study increasing recovery factors for these organs.Any prior thoracic radiotherapy < 6 months ago; OR prior thoracic radiotherapy delivered twice daily (compensation for holiday breaks are permitted), thoracic radiotherapy delivered by brachytherapy, radionuclides, proton beams, or electron beams.Plans for patient to receive daily adaptive radiotherapy in current plan (computed tomography [CT] or magnetic resonance [MR] based).Plans for the patient to receive other local therapy (including standard fractionated radiotherapy and/or surgery) while on this study, except at disease progression.Concurrent systemic therapy (i.e. on the same days as radiation) is not allowed, EXCEPT for patients being treated for intrathoracic lung cancer (non-small cell lung cancer [NSCLC] or small cell lung cancer [SCLC]) with curative intent.For other patients receiving systemic therapy, they are still eligible for enrollment as long as there is a break in systemic therapy during the course of radiation. For example, if a patient has been on palliative pemetrexed and is planning to continue, they can still be enrolled and would continue to receive pemetrexed; reirradiation would be delivered between cycles, possibly requiring a break in systemic therapy. See Sect. 6.9 for further details.Prior surgical intervention that has significantly changed the position of an organ-at-risk (OAR) that is expected to be a dose-limiting structure.PregnancyThe following autoimmune and connective tissue diseases will be excluded: scleroderma and systemic lupus erythematosus.Patients with interstitial lung disease (ILD).

### Pre-treatment evaluation and registration

See Appendix 1 for pre-treatment evaluation.

#### Registration

Complete the Enrollment Form in Research Electronic Data Capture (REDCap). Patient Study Number will be generated automatically upon completion of enrollment form in REDCap. Upload the de-identified consent form and signed Eligibility Checklist.Forward the pre-plan showing the total estimated accumulated dose in equivalent dose in 2 Gy fractions (EQD2) to organs-at-risk and dose contributions from each plan using the secure file transfer protocol (SFTP).All patients require an uploaded pre-plan to determine eligibility (i.e.to ensure that the model-assigned recovery factor is required to meet dose constraints). To assist with predicting eligibility, the principal investigators (PIs) will communicate the current dose level after every 4 patients enrolled; however, the dose level could change at any time due to newly reported outcomes.Notify the coordinating centre by phone or email that you have completed the enrollment form, uploaded the required documents, and the radiation plans have been sent for review.The coordinating centre will send an email to all sites with a reminder to report any new toxicities for previously enrolled patients, within 24 hours.PI will review the pre-plan and confirm eligibility and assign a dose level. If the patient is eligible the coordinating centre will confirm by email and inform sites of dose level assigned.Site will complete registration by going into REDCap and completing the registration form.In situations where the required recovery allowed by the trial (e.g. 25%) is more than required by the oncologist to deliver the prescribed treatment, those patients will not be registeredand they will be removed from the TITE-CRM model.

The flow chart in Fig. 1 illustrates the process.

**Fig. 1 Fig1:**
[figure not shown]
Trial flowchart

#### Example

 The desired current treatment is 30 Gy in 5 fractions to a lung lesion that overlaps the bronchus and will start mid-September 2024. There is expected prescription dose overlap (30 Gy in 5 fractions, 54.0 Gy EQD2/3) at the bronchus with a previous treatment of 60 Gy in 30 fractions, which ended January 31, 2024. In the area of overlap, the bronchus received a prior D0.1 cc = 45 Gy in 30 fractions (40.5 Gy EQD2/3).

Without any forgiveness, the total accumulated near-maximum dose to the bronchus in EQD2 will be: 40.5 EQD2Gy (prior) + 54.0 EQD2Gy (current) = 94.5 EQD2Gy, which is more than the limit of 80 EQD2Gy. This person would require 36% forgiveness against previous dose to meet the constraint.

The study PIs are contacted and note the current trial level is enrolling at Level 4. This would assign a recovery factor of 21% for this case (20% at 6 months plus 1% for an additional 7th month; partial months are not included). This is appropriate and the patient is enrolled. The Level 4 recovery factor is assigned and results in the previous dose contribution decreasing to 32 EQD2Gy. Note the bronchus would still be exceeding the dose constraint (total dose is 86 EQD2Gy) and planning target volume (PTV) would need to be partially compromised so that the bronchus dose is below 28 Gy in 5 fractions (48 EQD2Gy) to meet the 80 EQD2Gy constraint. The plan is adjusted, and treatment is delivered.

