#### Dosimetry

Treatment can be delivered using static beams (either 3D-conformal radiotherapy or intensity-modulated) or rotational therapy (volumetric modulated arc therapy, dynamic conformal arcs or tomotherapy). Single direct beams and parallel-opposed beam set-ups are not allowed. Only photon (x-ray) beams of 10 MV or less energy produced by linear accelerators will be used. Repeat CT and re-plans may be performed for gross changes in anatomy or set-up challenges; however, daily adaptive radiation therapy (ART) and MR linear accelator approaches are not allowed.

For the purposes of dose planning and calculation of monitor units (MUs) for actual treatment, this protocol will require tissue density heterogeneity correction.

Standard institutional dose constraints may be used for the current plan. Cumulative dose constraints listed in Table 2 may not be exceeded; these include both the current dose and the previous dose(s) scaled by the assigned recovery factor(s). Prescription de-escalation and/or target volume compromise is allowed at the discretion of the radiation oncologist to meet current plan and cumulative plan OAR dose constraints. The approach is context-dependent, but in general, this is usually pursued first by compromising PTV coverage, while maintaining GTV coverage, to a minimum dose the radiation oncologist feels to be clinically useful. If that is insufficient, consider decreasing dose and/or increasing number of fractions.

**Table 2 Tab2:** Organ-at-risk cumulative dose constraints in EQD2. D0.1 cc is the maximum dose in EQD2 allowable to the hottest 0.1 cc. V14.7EQD2Gy refers to the percent of Lung_eval (whole lungs minus all GTVs, trachea/ipsilateral bronchus) receiving 14.7 EQD2Gy or more (and is equivalent to a standard V20 using physical dose)

Contour name	α/β	Metric	Dose Limit
SpinalCanal or SpinalCord_PRV*	2	D0.035 cc	60 EQD2Gy
Brachial_Plexus	3	D0.1 cc	66 EQD2Gy
Esophagus	3	D0.1 cc	70 EQD2Gy
Heart or Heart_eval	3	D0.1 cc	80 EQD2Gy
Trachea	3	D0.1 cc	80 EQD2Gy
BronchialTree	3	D0.1 cc	80 EQD2Gy
GreatVessels	3	D0.1 cc	144 EQD2Gy
Chest Wall	3	D0.1 cc	180 EQD2Gy
Lung_eval	3	V14.7EQD2Gy	37%

^*****^Note: recovery factors assigned by the dose level in this trial do not apply to spinal cord. 60 EQD2Gy is allowed irrespective of dose level assigned by the trial. This limit may include 0–20% recovery of previous dose, at the discretion of the radiation oncologist. See example in Note under Evaluation of Accumulated Dose section

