#### Dose constraints

Table 2 lists near-maximum cumulative dose limits for several critical organs and volume constraints for lung. These are strict limits, and PTV coverage or prescription dose must be adjusted to meet them, if needed. These are mostly based on EQD2 conversions of the UK 2022 Consensus on Normal Tissue Dose-Volume Constraints for 5 fraction treatments [34]. The lung constraint is from RTOG 0617 (V20 in physical dose from the trial is equivalent to 14.7 Gy EQD2Gy) and so is the brachial plexus constraint [35]. The brachial plexus constraint of 60 EQD2Gy in the UK 2022 Consensus was felt to be too conservative because conventionally fractionated lung and head & neck protocols regularly use 66 Gy. There is no clear mandatory constraint for chest wall in the literature. This trial will use a chest wall constraint of 180 EQD2Gy; this is the equivalent of 60 Gy in 5 fractions, which is often allowed in lung SABR where PTV is not compromised for chest wall dose. The focus of this trial is on lung and mediastinal structure doses and escalation based on chest wall alone is not the goal of this protocol. Maximum point dose in undefined normal tissue should be kept as low as reasonably achievable, with a recommended limit of 200 EQD2Gy.

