**Table Tabb:**

Assigned Level	Time since Previous Treatment	Recovery Factor Calculation
Level 1	6 months	10 + 0 = 10%
Level 1	1 year	10 + [0.75% * (6 months)] = 14.5%﻿
Level 1	1 year and 3 weeks	Partial months not included; round down Recovery same as above, 14.5%
Level 1	10 years	No further repair after 5 years; apply 5 years for calculation 10 + [0.75% * ({5 years * 12 months/year} – 6 months)] = 50.5%^†^
Level 3	Two prior courses: Course 1 = 3 years ago Course 2 = 2 years ago	For course 1: 15 + [1% * ({3 years * 12 months/year} – 6 months)] = 45% For course 2: 15 + [1% * ({2 years * 12 months/year} – 6 months)] = 33%

^†^in practice, recovery values will be rounded to the nearest whole number so 14.5￫15% and 50.5￫51%

Example calculation for proximal bronchial tree dose at Level 1

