**Table Tabc:**

**Cou****rse**	**Physical Dose**	**EQD2****G****y**	**Recovery**	**Calculation**	**EQD2****G****y** **Applied to Cumulative Plan**
1 (previous course 1 year ago)	60Gy/30	60	15% (see calculation above)	60*0.85	51
2 (current course)	30Gy/10	36	0%	N/A	36
Total					87 < 88 EQD2Gy

*note point dose calculations are not sufficient for this trial; full 3D EQD2 dose evaluation based on dose distribution is required; the table above is for illustrative purposes of the dose scaling and dose constraint only

## Appendix 3

Calculated recovery factors per month

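### The Appendix 2 worked example passes a Level 1 proximal bronchial tree plan of 87 EQD2Gy against 88 EQD2Gy, but the binding Table 2 limit is 80 EQD2Gy

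*Protocol article*

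**What the plan says.** Table 2 (Dosimetry) lists "BronchialTree" with α/β of 3, metric D0.1 cc and a limit of 80 EQD2Gy. The text above it says "Cumulative dose constraints listed in Table 2 may not be exceeded". The Dose constraints section adds: "These are strict limits, and PTV coverage or prescription dose must be adjusted to meet them, if needed". The Quality assurance section makes compliance with Table 2, after forgiveness of prior dose, a requirement for every plan.

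The registration example uses the same limit twice for the bronchus. The total without forgiveness is one "which is more than the limit of 80 EQD2Gy", and the target volume is then compromised "to meet the 80 EQD2Gy constraint".

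Appendix 2 contains a table introduced as "Example calculation for proximal bronchial tree dose at Level 1". It takes a previous course of 60 Gy in 30 fractions (60 EQD2Gy) given one year ago, applies 15% recovery to leave 51 EQD2Gy, adds a current course of 30 Gy in 10 fractions (36 EQD2Gy), and shows the total of 87 as below 88 EQD2Gy. Its footnote warns that point-dose sums cannot replace a full 3D evaluation, and says that the table illustrates both the dose scaling and the dose constraint.

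**The concern.** The same organ carries two cumulative limits in the current text. The figure of 88 EQD2Gy appears only in Appendix 2; no row of Table 2 has it.

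This is more than a mistyped digit. The example's total sits 1.1% below 88 (1/88), which fits the Dosimetry advice to bring the dose-limiting organ within 3% of its limit without going over. If 88 is replaced by 80 and nothing else is changed, the printed inequality becomes false. The example has to be rebuilt.

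The threshold matters in this design because a recovery level has dosimetric meaning only together with the organ limit it is used to meet: the current dose permitted is the limit minus the scaled prior dose. A plan made to 88 would give the central airway more than its level number implies. Appendix 4 names the central airway among the organs of most concern.

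**Working it through.** **Inputs.** EQD2 = D(d + α/β)/(2 + α/β), from Evaluation of accumulated dose, with α/β = 3 and the 80 EQD2Gy limit from Table 2. Doses and timing are from the Appendix 2 example. Recovery at 12 months by level is from Appendix 3.

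**Reproducing the article's figures.**
- Previous course: 60 × (2 + 3)/5 = 60 EQD2Gy.
- Current course: 30 × (3 + 3)/5 = 36 EQD2Gy.
- Level 1 at 12 months: 10 + 0.75 × 6 = 14.5%, rounded to 15%.
- Total: 60 × 0.85 + 36 = 87.0 EQD2Gy, as printed (87.3 with the unrounded 14.5%).
- Registration example: 40.5 + 54.0 = 94.5; required recovery (94.5 − 80)/40.5 = 35.8%, stated as 36%; at 21% recovery, 40.5 × 0.79 + 54.0 = 86.0. These also match.

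The dose sums in both examples are correct. Only the comparison figure in Appendix 2 is wrong.

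**Testing the Appendix 2 plan against 80 EQD2Gy.**
- Excess: 87 − 80 = 7 EQD2Gy; 7/80 = 8.75%.
- Recovery needed: (60 + 36 − 80)/60 = 16/60 = 26.7%.

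Totals at 12 months, 60 × (1 − recovery) + 36:

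| Level | Recovery | Total (EQD2Gy) | At or below 80? |
|---|---|---|---|
| −1 | 6% | 92.4 | no |
| 0 | 13% | 88.2 | no |
| 1 | 15% | 87.0 | no |
| 2 | 20% | 84.0 | no |
| 3 | 21% | 83.4 | no |
| 4 | 26% | 80.4 | no |
| 5 | 28% | 79.2 | yes |
| 6 | 33% | 76.2 | yes |

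With the unrounded 27.5%, Level 5 gives 79.5, so rounding does not change the result.

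**What Level 1 allows under Table 2.** Current bronchial dose at most 80 − 51 = 29 EQD2Gy. Solving D(D/10 + 3)/5 = 29 gives D ≈ 25.9 Gy in 10 fractions, against the 30 Gy in the example.

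**How far the Level 5 result carries.** It depends on the interval. With the same doses and the prior course 36 months ago, Level 1 gives 33% and a total of 60 × 0.67 + 36 = 76.2, which complies. At 6 months even Level 6 (25%) gives 60 × 0.75 + 36 = 81.0, which does not.

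**The case against.** The strongest reply is that the governing limit is not in doubt. Table 2 sets 80, three sections make it binding, and the registration example applies it. Appendix 2 is cited in Evaluation of accumulated dose for example calculations, not as a source of limits. There are also checks: a principal investigator reviews each pre-plan and confirms eligibility, accumulated dose is peer-reviewed locally, and a physicist or oncologist verifies organ doses before plan approval. Nothing in the article shows that any patient was planned to 88.

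Most of this stands, and it limits the point. It does not excuse the number: the footnote says the table illustrates the dose constraint, and that is the element that is wrong.

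Three stronger readings are tempting and are not supported.

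- A reader might infer that the example fails under 88 as well, because (96 − 88)/60 = 13.3% is less than the 15% assigned and the patient would not be registered, or that the registration example's patient would change eligibility under 88. The exclusion criterion on cumulative dose refers to all organs-at-risk, and both examples report only the bronchus. Another organ could still need the assigned factor.
- A reader might infer that Level 1 in this trial generally means a Level 5 dose to the airway. That equivalence belongs to one hypothetical case, and Level 4 misses by only 0.4 EQD2Gy.
- A reader might infer that the TITE-CRM data are already distorted. That would need patients whose bronchial tree is dose-limiting to have been planned to 88, and no such deviation is documented.

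**Conclusion.** Wrong as written, and should be fixed. The Appendix 2 example presents as compliant a plan that exceeds the binding bronchial tree limit by 7 EQD2Gy (8.75%). In that example the plan first meets the limit at Level 5. This rests on Table 2 being the intended rule, which the text supports at every other place, and on taking the example's doses at face value as D0.1 cc values. The stated constraint, the eligibility rule, the MTD definition and the model are unaffected. The risk is that a planner copies a permissive threshold from a worked example; the pre-plan review and local checks reduce that risk.

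**What to change.** 1. In Appendix 2, change 88 to 80 EQD2Gy and rework the example so that it complies at Level 1, with a current bronchial dose of at most 29 EQD2Gy (about 25.9 Gy in 10 fractions) for the same prior course and interval.
2. Send sites a short memo stating that Table 2 governs and that the Appendix 2 figure was an error.
3. When uploaded plans are reviewed, confirm that BronchialTree D0.1 cc was held to 80 EQD2Gy. A TITE-CRM sensitivity analysis is needed only if a deviation is found.

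The cost is one corrected figure, a reworked example, a memo, and one item added to the review of plans already collected. No patients are added.
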